#### Analysis populations

##### Intention-to-treat population

The intention-to-treat population contains all patients who have participated in visit 2 (surgery), independent of the intervention they receive (control or NPIT). Analysis will occur as randomized. Patients who unexpectedly receive a laparoscopic or laparoscopic assisted operation (exclusion criterion) will be excluded from the intention-to-treat population. Missing primary endpoint data in the intention-to-treat population will be treated as follows: data missing because of death or relaparotomy will be counted as surgical site infection in both groups. Data missing for other reasons (e.g., lost to follow-up) will not be counted as surgical site infection in either group.

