### Sample size

A total of 152 patients will be analyzed per group. Given an estimated drop-out rate of approximately 10 %, 340 patients will be randomized to the two treatment arms.

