### Statistical methods

#### Sample size calculation

Sample size calculation is based on the primary endpoint measure (whether or not there is surgical site infection, according to CDC) within 30 days post operation [9] and was conducted by using nQuery Advisor® software version 7.0 (Statistical Solutions Ltd, Cork, Ireland). Based on the assumption that the percentage of patients developing postoperative wound infections in a surgical population undergoing open colorectal surgery is approximately 25 % for the control group (based on results from previous randomized controlled trials in abdominal surgery [14, 15, 17]) and can be reduced to 12.5 % in the experimental intervention arm, a group sample size of 152 patients would need to be compared using the chi-square test, to achieve 80 % power in detecting this difference in surgical site infection rate at a two-sided level of significance of 5 %. Under the assumption of a drop-out rate of up to 15 %, a total of 340 patients (170 per group) need to be enrolled in the study. Owing to the broad inclusion criteria and the limited number of exclusion criteria, the limited study time per patient (30 days), as well as the comprehensible nature of the trial, no more than 100 patients are expected to fail the screening process. Therefore, the total number of patients needed for screening is 440 (Fig. 1).

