## Discussion

Postoperative surgical site infections are amongst the most frequent surgical complications, affecting approximately 14 % to 32 % of patients undergoing abdominal surgery [18, 42, 43]. These numbers have changed little over the last 20 years despite internationally accepted recommendations for control of surgical site infections (reviewed in [44]). In prospective trials with clear definitions, surgical site infection rates above 15 % have frequently been reported [13–16, 18] and are especially high in colorectal surgery [14, 15, 17]. Applying standard definitions for surgical site infections is crucial, as a number of surgical site infections occur after discharge of patients from the hospital and would thus remain unnoticed if standardized wound evaluation, as well as adequate follow-up, were not applied. Unfortunately, numerous different surgical site infection definitions have been proposed [45], albeit the surgical site infections definition of the CDC has gained wide acceptance over past decades [9]. According to this definition, surgical site infections are grouped into superficial, deep and organ-space surgical site infections that occur within 30 days of the operation (Table 1).

The most frequent pathogens causing postoperative surgical site infections in general surgical patients are *Staphylococcus aureus*, *Escherichia coli* and *Enterococcus* species. Similarly, in abdominal surgical patients, *E. coli*, *Enterococcus* species, *Enterobacter* species and *S. aureus* are the most frequently pathogens isolated from wounds [7]. These data indicate that endogenous contaminations from the patients’ skin or the gastrointestinal tract occurring during surgery account for most surgical site infections. Therefore, a considerable number of surgical site infections might be prevented by draining contaminated wound secretions from the incisional site during the early postoperative period. Negative-pressure incision therapy devices (Fig. 2) have been designed to drain wound secretions from the postoperative wound. The feasibility and safety of NPIT devices has been demonstrated in several studies [28–32, 34], but their efficacy has not yet been tested in multicentre randomized controlled trials. However, previous studies were single-centre trials, lacked clear surgical site infection definitions and endpoint measures, or included only few patients [36]. Furthermore, no data exists on the efficacy of NPIT devices in abdominal surgery.

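### The primary analysis scores patients with missing endpoints as infection-free, which does not match the dropout allowance and can create a false difference if loss is unequal between arms

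*Protocol article*

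**What the plan says.** The primary endpoint is analysed in the intention-to-treat population, which takes in all patients who underwent the operation visit, apart from those who unexpectedly had laparoscopic surgery. Under the heading Intention-to-treat population, an endpoint missing through death or relaparotomy counts as an infection. For the rest: "Data missing for other reasons (e.g., lost to follow-up) will not be counted as surgical site infection in either group". Lost patients therefore stay in the denominator as non-events.

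The Sample size calculation assumes that the infection rate "is approximately 25 % for the control group", and that with the device it "can be reduced to 12.5 % in the experimental intervention arm". For these rates the stated requirement is that "a group sample size of 152 patients would need to be compared using the chi-square test"; the target is 80% power with a two-sided 5% test. This is enlarged to 170 per group for dropout of up to 15%. The Sample size section under Methods/Design gives the same total of 340 with dropout of about 10%, and adds: "A total of 152 patients will be analyzed per group".

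The Sensitivity analysis section repeats the primary analysis in the per-protocol and surgical site infection populations. It places three imputation schemes, (a) to (c), in the latter, which is defined as patients who reached visit 6.

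**The concern.** The two parts of the plan treat a lost patient differently. The sample size removes the patient and keeps the full rates. The primary analysis keeps the patient and enters a non-event. The number analysed is then 170 rather than 152, at rates lower than those the power was calculated for.

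The rule also sits badly with the reason given for 30-day follow-up. The Discussion says that "a number of surgical site infections occur after discharge of patients from the hospital and would thus remain unnoticed" without standardized wound evaluation and adequate follow-up. Scoring a patient without that follow-up as infection-free makes the same error by rule, and it enters a guess as if it were an observation.

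The direction of the comparison is also at stake. The Randomization and blinding section concedes that patients cannot be blinded, because the device looks different from an ordinary dressing. Loss may then differ by arm, and the arm that loses more patients gains more imputed non-events.

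**Working it through.** **Inputs.** Control rate 25%, device rate 12.5%, two-sided 5%, chi-square test, 152 evaluable and 170 randomized per group, dropout about 10% or up to 15% (Sample size; Sample size calculation).

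**Step 1: reproduce the plan's figure.** With p̄ = 0.1875,

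n = [1.960·√(2p̄(1−p̄)) + 0.842·√(p₁(1−p₁) + p₂(1−p₂))]² / (p₁−p₂)²
= [1.960 × 0.5520 + 0.842 × 0.5449]² / 0.125² = 151.9, so 152 per group. The stated figure is right.

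Dropout allowance: 152/0.90 = 168.9, so 169, which 170 covers. 152/0.85 = 178.8, so 179, which 170 does not cover.

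**Step 2: apply the scoring rule.** Assume that loss d is the same in both arms, is unrelated to infection, and that no infection is recorded before loss. The analysed rates become 25%·(1−d) and 12.5%·(1−d) with n = 170. Power = Φ[(Δ − 1.960·s₀)/s₁], where Δ is the difference in rates and s₀ and s₁ are the pooled and unpooled standard errors.

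- d = 10%: 22.5% v 11.25%, Δ = 0.1125, s₀ = 0.0406, s₁ = 0.0402; power 79.4%.
- d = 15%: 21.25% v 10.6%, Δ = 0.10625, s₀ = 0.0397, s₁ = 0.0393; power 76.5%.

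**Step 3: separate the rule from the dropout allowance.** Leave the lost patients out and keep 25% v 12.5%.

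| Loss | Lost left out | Lost = no infection | Cost of the rule | n per group for 80% under the rule |
|---|---|---|---|---|
| 10% | 80.3% (n = 153) | 79.4% | 0.9 points | 173 |
| 15% | 78.0% (n = 144.5) | 76.5% | 1.5 points | 186 |

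At 15% the shortfall from 80% is 3.5 points: 2.0 because 170 is too few for 15% dropout, and 1.5 from the rule.

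**Step 4: effect size under equal loss.** The absolute difference falls from 12.5 to 11.25 points (10% loss) or 10.6 points (15% loss). The factor (1−d) cancels in the risk ratio, which stays 0.50.

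**Step 5: unequal loss.** The document gives no loss by arm, so the splits below are assumptions.

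- No true effect, 25% in both arms, 15% lost on the device and 5% on control: 0.25 × 0.85 = 21.25% v 0.25 × 0.95 = 23.75%, a false benefit of 2.5 points. With s₀ and s₁ both about 0.0453, the chance of a significant result is Φ(−1.41) + Φ(−2.51) = 7.9% + 0.6% = 8.5%, against a nominal 5%.
- True effect as planned, same split: 10.6% v 23.75%, risk ratio 0.45 instead of 0.50.
- True effect as planned, reverse split: 11.9% v 21.25%, risk ratio 0.56, power 64.4%.

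**Step 6: do the sensitivity analyses test the rule?** Schemes (a) to (c) impute missing endpoints among patients who reached visit 6. Patients lost before visit 6 are outside that set, so little or nothing remains to impute. The per-protocol and surgical site infection repeats also leave these patients out. As written, no analysis assigns an infection to a patient lost to follow-up.

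**The case against.** The strongest reply is that the rule is explicit, prespecified and the same in both arms, and that it costs about one point of power at the 10% dropout figure. That is correct. A reader might infer that the trial therefore lacks its stated 80% power. The figures do not support this at 10% loss, where 79.4% is essentially 80%. At 15% most of the shortfall comes from the dropout allowance.

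Second, the rule concerns missing endpoints only. Table 2 records infection at days 5–7 and 9–11, at discharge and at optional visits, and nothing says that an infection already recorded would be discarded when the patient is later lost. If half of the lost patients' infections were recorded beforehand, power would be 81.9% at 10% loss and 80.7% at 15%. This stands, and the figures in Step 2 are the unfavourable end. The text does not state the point, however, and should.

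Third, a reader might infer that the reported infection rates will be too low overall. That does not follow. The companion rule counts endpoints missing through death or relaparotomy as infections and pushes rates up, so the net direction depends on the mix of reasons. Larger power losses can be obtained by assuming a share of such patients, but the document gives no such share, so they are not relied on here.

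Fourth, the repeats among patients who completed follow-up do avoid the rule. If loss is unrelated to infection, a gap between them and the primary result would give some warning. They would not correct the primary result, and they say nothing about loss that is related to infection.

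**Conclusion.** The concern holds in a limited form. The missing-data rule and the dropout allowance are inconsistent, and the rule conflicts with the protocol's own case for complete follow-up. Under equal loss the cost is modest: 0.9 points of power at 10% loss and 1.5 at 15%, a smaller absolute difference, and an unchanged risk ratio. The power stated for dropout of up to 15% is not delivered (about 76.5%), mainly because 170 per group is too few for that dropout.

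The reason to act is bias under unequal loss. With no true effect, a 15% v 5% split turns the nominal 5% error into about 8.5%, and the planned imputations are placed where they cannot show it.

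These results assume that loss is unrelated to infection, that no infection is recorded before loss, and that power is that of the unadjusted chi-square test used in the protocol's calculation. The planned analysis is a logistic regression with centre and baseline terms. The size and direction of any imbalance in loss are unknown.

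**What to change.** 1. In the primary intention-to-treat analysis, state that any infection documented before loss counts as an event. For patients lost without a recorded infection, use multiple imputation by arm, with baseline factors and the time of the last wound assessment.
2. Keep the present scoring of lost patients as infection-free as a sensitivity analysis.
3. Move imputation schemes (a) to (c) from the surgical site infection population to the intention-to-treat population, where there are missing endpoints to impute. Scheme (b) then largely serves as item 2.
4. Settle on one dropout figure. If the current rule is kept for the primary analysis, restate power as about 79% at 10% loss and about 76–77% at 15%.

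The cost is a change of wording and slightly more analysis work, with no new data. Multiple imputation brings its own assumption, that data are missing at random given the variables used, and the relocated schemes (a) to (c) would probe it.

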##### Per-protocol population

The per-protocol population contains all patients included in the intention-to-treat population as treated (not as randomized). The following patients will be excluded: (a) patients who receive a surgical wound dressing that is not predefined in the randomization scheme (i.e., neither an NPIT system nor a standard sterile dressing); (b) patients who do not reach visit 6 for reasons other than death or relaparotomy. Patients who die or undergo relaparotomy will be counted as having surgical site infections in both groups.

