#### Experimental intervention

Patients undergoing open colorectal procedures and randomized to the experimental arm will have the full length of their incision covered with an NPIT device (Prevena Incision Management System, KCI, Inc., San Antonio, TX, USA) starting in the operating room right after closure of the skin incision (see Fig. 2). In the intervention group, the NPIT system should cover the surgical wound for a minimum of 5 days and a maximum of 7 days (till postoperative day 5–7; visit 2; see Table 2). If the NPIT system is removed prior to postoperative day 5–7 (event visit; see Table 2) the reasons must be documented and a new NPIT system has to be applied to ensure coverage of the wound for 5–7 days after the operation. The reasons for a definite removal of the NPIT system prior to postoperative day 5–7 must be documented and state whether there is a surgical site infection (the primary endpoint measure of the trial) or whether the NPIT system is not tolerated by the patient.

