#### Sensitivity analysis of the primary endpoint measure

The primary endpoint analysis will be repeated in the per-protocol and surgical site infection population. Further sensitivity analyses will be performed as follows: (a) in the surgical site infection population, all missing data will be imputed as surgical site infections in both groups; (b) in the surgical site infection population, all missing data will be imputed as non-surgical site infection in both groups; (c) in the surgical site infection population, missing data will be imputed as surgical site infections in the intervention group, but as non-surgical site infection in the control group; (d) a time-to-event analysis will be performed in the surgical site infection population according to Kaplan–Meier analysis.

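### The set labelled per-protocol is an as-treated set that moves crossovers to the other arm, and two of its event rules differ from those of the primary analysis

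*Protocol article*

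**What the plan says.** The Per-protocol population section sets four rules.

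- Grouping: "The per-protocol population contains all patients included in the intention-to-treat population as treated (not as randomized".
- Exclusion (a), by type of dressing: "patients who receive a surgical wound dressing that is not predefined in the randomization scheme (i.e., neither an NPIT system nor a standard sterile dressing".
- Exclusion (b), by follow-up: "patients who do not reach visit 6 for reasons other than death or relaparotomy".
- Scoring: "Patients who die or undergo relaparotomy will be counted as having surgical site infections in both groups".

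For the primary analysis, the Intention-to-treat population section says "Analysis will occur as randomized" and that "data missing because of death or relaparotomy will be counted as surgical site infection in both groups". Endpoints missing for other reasons count as no SSI.

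The Sensitivity analysis section links the two sets: "The primary endpoint analysis will be repeated in the per-protocol and surgical site infection population". Table 2 has SSI documented at visits 3, 4, 5 and 6 and at an optional visit, so an event can be on record well before visit 6.

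**The concern.** A per-protocol analysis normally asks what happens among patients who received what they were allocated. Here the only dressing-related exclusion is for patients who received neither study dressing. A patient who received the other arm's dressing is neither removed nor left in the randomised arm, but counted in the opposite arm. That is an as-treated comparison. It loses the protection of randomisation and is unbiased only if the patients who cross over carry the same SSI risk as everyone else.

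Two further rules make the analysis something other than the primary analysis repeated. Exclusion (b) can delete known events, and the scoring sentence can turn an observed non-event into an event. If the result differs from the ITT result, a reader will be unable to tell which of these changes produced the difference.

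**Working it through.** **1. The rules applied to individual patients**

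| Patient | ITT (primary) | Per-protocol as written |
|---|---|---|
| Randomised to NPIT, received standard dressing, reached visit 6 | NPIT arm | Control arm |
| SSI documented at visit 3, then missed visit 6 by withdrawal | Event (endpoint already met, not missing) | Excluded by (b) |
| Relaparotomy, wound assessed to visit 6, no SSI by CDC criteria | Non-event | Event |
| Death or relaparotomy, endpoint missing for that reason | Event | Event |

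The first three rows differ and the fourth agrees. The endpoint mismatch is therefore confined to patients with a relaparotomy (rarely, a death) whose outcome was assessed and SSI-free. It is narrower still because Table 1 already counts infection found at reoperation as SSI.

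**2. The plan's own figure**

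The Sample size calculation section gives 152 per group for 25% v 12.5%, two-sided 5%, 80% power, chi-square test. With pooled variance:

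n = [1.960 × √(2 × 0.1875 × 0.8125) + 0.842 × √(0.25 × 0.75 + 0.125 × 0.875)]² / 0.125² = (1.082 + 0.459)² / 0.015625 ≈ 152.

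The figure reproduces, with power 80.0% at 152. It belongs to the primary ITT test and does not depend on how the per-protocol set is defined.

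**3. How much bias switching arms can cause**

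Inputs: SSI risk p = 25% (the article's control rate) in both randomised arms, so no true effect; 170 per group (from the article). Assumptions, because the article gives no crossover rate: a share x of the NPIT arm, with SSI risk q, receives the standard dressing; nobody crosses the other way; nobody is lost.

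- NPIT as treated = (p − xq)/(1 − x)
- Standard as treated = (p + xq)/(1 + x)
- Difference (standard minus NPIT) = 2x(q − p)/(1 − x²)

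For x = 10%, q = 50%: each arm has 170 × 0.25 = 42.5 events, and 17 patients with 8.5 events move. NPIT = (42.5 − 8.5)/153 = 34/153 = 22.2%. Standard = (42.5 + 8.5)/187 = 51/187 = 27.3%. The difference is 5.1 points (RR 0.81) where the truth is zero.

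| x | q | NPIT | Standard | Difference |
|---|---|---|---|---|
| 5% | 50% | 23.7% | 26.2% | 2.5 points |
| 10% | 75% | 19.4% | 29.5% | 10.1 points |
| 10% | 25% | 25.0% | 25.0% | 0 |
| 10% | 10% | 40.8/153 = 26.7% | 44.2/187 = 23.6% | −3.0 points |

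The direction is open: bias favours NPIT if higher-risk patients leave that arm and goes against NPIT if lower-risk patients leave it.

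**4. What excluding crossovers achieves**

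The NPIT rate stays (p − xq)/(1 − x) and control stays p, so the difference is x(q − p)/(1 − x). At x = 10%, q = 50% this is 22.2% v 25.0%, or 2.8 points (RR 0.89). The ratio to the switched analysis is (1 + x)/2 = 0.55, so a little over half the bias remains.

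**The case against.** The strongest reply is that little depends on this set. The primary analysis is ITT and as randomised, the per-protocol repeat is one of several sensitivity analyses, and the as-treated grouping is disclosed. That stands, and it limits the weight of the point.

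The scoring sentence directly follows exclusion (b) and may only say how the patients whom (b) spares are to be scored, which would be the ITT rule again. That is a fair reading. A reader might go further and infer that the set tests a different endpoint, so that agreement or disagreement with ITT means nothing. The documents do not support this: the rules coincide wherever the endpoint is missing through death or relaparotomy, and the remainder may be only a wording mismatch.

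A reader might also infer a substantial loss of power from scoring deaths and relaparotomies as SSI. That does not follow. The comparison would be with no recoding at all, whereas ITT already recodes the missing cases. The article gives no relaparotomy or death rate, and 152 per group was sized for the primary test.

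It is tempting, too, to treat the retention of NPIT patients whose device came off early as a defect, since "the NPIT system should cover the surgical wound for a minimum of 5 days and a maximum of 7 days". But the same section foresees replacement devices and documented definite removal, keeping such patients is defensible in a trial described as pragmatic, and an exposure threshold can be left to the analysis plan.

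Finally, it cannot be taken as fact that crossover will follow risk. Randomisation takes place in theatre after skin closure and the device is applied at once, which leaves little time for the wound's course to steer the first dressing. The concern is conditional on such a link.

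**Conclusion.** The concern holds in a limited form. As written, the per-protocol set is an as-treated set, so the planned sensitivity analysis does not estimate a per-protocol effect. It is biased if crossover is related to SSI risk. The documents do not allow the size to be estimated; under the assumptions shown it ranges from zero (crossovers of average risk) to about 10 points (10% crossover at 75% risk), in either direction.

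Separately, exclusion (b) taken literally deletes SSIs documented before a missed visit 6. The death and relaparotomy sentence also makes an assessed, SSI-free relaparotomy patient an event here but a non-event in ITT. The primary ITT test, its type I error and its power are unaffected. The definitions should be corrected before the data are analysed, but the trial's main conclusion does not depend on them.

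**What to change.** Reword the Per-protocol population section as follows.

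- Include ITT patients who received their allocated dressing, analysed in their randomised arm.
- Exclude crossovers instead of switching them, and state that some selection bias remains.
- Keep a patient whose SSI was documented before loss to follow-up as an event; apply exclusion (b) only where no SSI is on record.
- Use the ITT rule for death and relaparotomy, including its missing-data condition, so that both sets score the same patient alike.
- If an as-treated analysis is wanted, list it separately under that label.

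If adherence to device coverage is later added as a criterion, it must not depend on the outcome. Excusing short coverage only when an SSI ended it would keep early removals with an event and drop those without one, which biases against NPIT.

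The cost is a change of wording and a per-protocol set smaller by the number of crossovers. It needs only the dressing each patient received and the SSI documentation already scheduled in Table 2.

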##### Surgical site infection population

The surgical site infection population contains all patients included in the intention-to-treat population who have reached the study end (visit 6), independent of the treatment they have received (‘as randomized’).

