#### Analysis of the primary endpoint measure

The analysis of the primary endpoint measure will be performed in the intention-to-treat population. The statistical hypothesis is:$$ {H}_0:{\varPi}_{\mathrm{T}}={\varPi}_{\mathrm{C}}\kern1em \mathrm{versus}\kern1em {H}_{\mathrm{A}}:{\varPi}_{\mathrm{T}}\ne {\varPi}_{\mathrm{C}} $$where Π_T_ is the rate of surgical site infections in the NPIT group and Π_C_ the rate of surgical site infections in the control group. Rates of surgical site infection will be analyzed via multivariate binary logistic regression with centre effects and possible baseline differences between intervention and control group. The level of significance will be set at 5 %.

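### The per-protocol set keeps patients given the other arm's dressing and counts them in that arm, so this sensitivity analysis is an as-treated comparison under a per-protocol label

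*Protocol article*

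**What the plan says.** All references are to the protocol article, Statistical methods.

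- **Per-protocol population.** The set is built from the intention-to-treat set, but patients are grouped by what they received: "The per-protocol population contains all patients included in the intention-to-treat population as treated (not as randomized"). There are two exclusions. The first covers a dressing outside the randomisation scheme, which the text spells out as "i.e., neither an NPIT system nor a standard sterile dressing". The second covers "patients who do not reach visit 6 for reasons other than death or relaparotomy".
- **Sensitivity analysis of the primary endpoint measure.** This set has a stated role: "The primary endpoint analysis will be repeated in the per-protocol and surgical site infection population".
- **Surgical site infection population.** The other set named there keeps the randomised groups: "independent of the treatment they have received (‘as randomized").
- **Intention-to-treat population and primary analysis.** "Analysis will occur as randomized", and "The analysis of the primary endpoint measure will be performed in the intention-to-treat population".

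**The concern.** A patient randomised to NPIT who receives a standard dressing, or the reverse, has not followed the allocation. Neither per-protocol exclusion removes that patient, because the dressing received is one of the two study dressings. The as-treated rule then moves the patient to the other arm. The resulting set is not per-protocol in the usual sense, since it contains patients who broke their allocation. It is not randomised either, since group membership depends on what was done after randomisation.

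If crossovers differ from other patients in infection risk, regrouping acts on both sides of the comparison: their risk leaves one arm and enters the other. Excluding them acts on one side only. What is at stake is how far a prespecified sensitivity analysis can be trusted, and whether its label tells readers what was compared.

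**Working it through.** **1. Follow a crossover through the rules.** Take a patient randomised to NPIT who leaves theatre with a standard dressing and completes visit 6.
- Intention-to-treat: counted in the NPIT arm.
- Surgical site infection population: counted in the NPIT arm.
- Per-protocol: not removed by the dressing exclusion (a study dressing was used) and not removed by the visit 6 exclusion. Counted in the control arm.

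The reverse crossover is handled in the same way. No other section removes either patient.

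**2. Inputs for size.**
- From the Sample size calculation section: control rate 25%, 152 analysed per group, two-sided 5% level, chi-square test. These are consistent with one another: for 25% v 12.5% at 80% power, the pooled-variance formula without continuity correction returns 152 per group (power 80.0%).
- Assumed, because the document gives no figure: no true effect (25% in both arms, so 0.25 × 152 = 38 expected infections per arm), crossover in one direction only, k = 8 or 15 crossovers (about 5% or 10% of an arm), and infection risk r = 50% in those patients.

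**3. Expected rates, crossover from NPIT to standard dressing.**
- As treated, NPIT: (38 − k·r)/(152 − k). As treated, control: (38 + k·r)/(152 + k).
- k = 8: 34/144 = 23.6% v 42/160 = 26.3%; risk ratio 0.90.
- k = 15: 30.5/137 = 22.3% v 45.5/167 = 27.2%; risk ratio 0.82.
- Crossovers excluded, with control staying at 38/152 = 25%: 23.6% v 25% (risk ratio 0.94) and 22.3% v 25% (risk ratio 0.89).
- Difference as treated against excluded: −2.6 against −1.4 points (k = 8) and −5.0 against −2.7 points (k = 15). As-treated grouping carries about 1.8 to 1.9 times the bias of exclusion.

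**4. Chance of a false significant NPIT benefit** (simulated trials, pooled z test, same assumptions).

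| Grouping | 8 crossovers | 15 crossovers |
|---|---|---|
| As treated | about 7.5% | about 16% |
| Crossovers excluded | about 4.6% | about 7.7% |
| As randomised | 2.5% | 2.5% |

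**5. Other directions and risks.**
- Standard to NPIT: the rates swap, to 26.3% v 23.6% and 27.2% v 22.3% against NPIT. The chance of a false NPIT benefit falls to 0.7% and 0.1%, and the 7.5% and 16% become chances of false harm.
- Equal crossover both ways: false benefit 2.5% and 2.4%, essentially nominal.
- r = 40% with 15 crossovers from NPIT to standard: 8.5% as treated, 5.0% excluded.
- r = 25%, or no crossover: no bias.

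**The case against.** The strongest reply is that little depends on this set. A reader might infer that the rule could make a non-existent NPIT effect look confirmed. The calculations do not support that. The primary analysis is intention-to-treat, so false confirmation first needs a falsely significant primary result. In the scenarios above, the chance that the primary analysis and the as-treated set both show a false benefit is about 2.4%, and about the same with crossovers excluded. The 7.5% and 16% are chances for this set taken alone. Its more likely effect is a per-protocol result that disagrees with a null primary result. This part of the reply stands.

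Three further limits also stand:
- A reader might take this to be the main supportive analysis. The sensitivity section does not rank it above the surgical site infection population, which keeps the randomised groups.
- A reader might infer a bias in favour of NPIT. No section says which direction of crossover would prevail, how often it would occur or why. Allocation is opened in theatre after skin closure, by staff who know the operation, so a link with risk is plausible. It remains an inference.
- Excluding crossovers does not restore a randomised comparison; it reduces the bias in these scenarios.

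It can also be said that the grouping is stated openly, so no one is misled. That answers only part of the point. A reader of the methods can see the rule, but a reader of a result labelled per-protocol will normally assume that each patient received the assigned dressing.

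**Conclusion.** The point holds as a flaw in the definition of one prespecified sensitivity analysis. The text fixes an as-treated grouping, keeps crossovers and calls the result per-protocol. The primary analysis and its error rate are untouched.

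The size is conditional. With 8 or 15 one-way crossovers at twice the average risk and no true effect, the spurious difference is about 2.6 or 5.0 percentage points, in a direction set by the direction of crossover. That is nearly twice the difference left when the same patients are excluded. With no crossover, or crossover unrelated to risk, there is no bias and only the mislabelling remains.

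**What to change.** Redefine the per-protocol population as intention-to-treat patients who received the dressing they were randomised to, analysed in the randomised arm. Patients given the other arm's dressing are excluded, alongside the exclusions already listed. If an as-treated analysis is also wanted, list it separately under that name as exploratory. Make the change before unblinding, so that the choice cannot appear to follow the data.

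The cost is one changed sentence, plus a line for any as-treated analysis. A few patients leave one sensitivity analysis, and the resulting set is still not fully protected by randomisation, which the report should say. The sample size, data collection and primary analysis do not change.
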